### Study Protocol Design

The present clinical study protocol describes a single-blind randomized controlled trial comparing 4 weeks of RAT using the NEEM robotic elbow exoskeleton to a control group receiving a matched volume of conventional physiotherapy. The primary outcome measures are the Modified Ashworth Scale (MAS) and the upper-extremity Fugl-Meyer Assessment (FMA) scale, two standard clinical scales used to assess upper-limb spasticity and functionality in neurological patients. Subjects are randomly assigned either to the control group (CG), or to the treatment (robotic) group (TG). Both groups will receive a conventional 4-week upper-limb physiotherapy program, consisting of repeated elbow flexion/extension movements: control group patients will focus on manual mobilizations of the limb while aided by the therapist, while the robotic group will receive the same net treatment volume via the robotic device. The treatment group will be further divided into two levels (sub-groups), based on pathological severity: Level 1 corresponds to an FMA score equal or below 28, and Level 2 with FMA >28. The two sub-groups will receive different combinations of robotically assisted *passive* and *active* mobilization treatment modalities, according to their differing clinical needs. Level 1 therapy is designed for patients with very low residual mobility, focusing on *passive mobilization* of the affected limb using a *robot-in-charge* control paradigm (29), where the robot moves the user's arm through a pre-defined spatio-temporal trajectory without requiring his/her active contribution, so as to entrain desired movement patterns and/or reduce joint stiffness (including spasticity). In addition to passive mobilization, Level 1 participants will also perform a limited number of *active mobilization* exercises, using a *patient-in-charge* paradigm (29) in which the user initiates and follows defined movement trajectories, receiving robotic assistance only *as-needed*. According to their higher motor function at baseline, Level 2 subjects will perform a greater proportion of active mobilizations relative to passive exercises (3:1), to emphasize the development of upper limb strength and motor control. Subjects in both treatment sub-groups will also be evaluated for their voluntary movement capacity in each session, via a brief bout of active movements performed with the robotic device in *transparent* (unassisted) mode.

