### Participants and Recruitment

All procedures conform to the Declaration of Helsinki and have been approved by the Ethical Committee for the Azienda USL Toscana Nord Ovest (AUSLTNO) and the Italian Ministry of Health.

The study is conducted at the Recovery and Functional Rehabilitation department of Ospedale Versilia (Lido di Camaiore, Italy), in collaboration with The BioRobotics Institute of Scuola Superiore Sant'Anna. It involves 60 post-stroke patients with right-sided hemiplegia, randomly allocated either to the control (*n* = 30) or treatment (*n* = 30) group. The sample size of each group was calculated based on the hypothesis of a post-treatment MAS score reduction of 0.5 points (compared to pre-treatment, from an average of 2.5 ± 0.70 SD at baseline) with an alpha value of 0.05 and power equal to 80%. (30).

According to inclusion criteria, patients should: (1) be in the age range 18–79; (2) have sustained unilateral hemorrhagic or cerebro-vascular ischemic event in sub-acute (< 6 months) or chronic (> 6 months) phase; (3) experience a functional motor deficit of the right arm (ranging from mild to severe hemiplegia or paresis); (4) have residual cognitive capabilities sufficient for the understanding of basic instructions (Mini-Mental State Examination score > 24); (5) exhibit lack of pain upon passive mobilization of the limb; (6) be able to sign an informed consent. On the contrary, patients are excluded from the study in case of: (1) unstable state of general health; (2) inability to remain in a seated position for a prolonged period (1 h or more); (3) use of a cardiac pacemaker or other active implanted medical devices; (4) passive range of motion (ROM) lower than 10 degrees. In addition, patients who received botulinum toxin injections within 3 months prior to the participation to the study or individuals who follow any additional pharmacological treatment that may alter the outcome of the study are excluded from the participation to the study. Sudden changes in subjects' health conditions, severe alterations in their psychophysical well-being or the inability to attend more than three daily consecutive sessions will lead to the exclusion from the study.

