Patients are recruited from across Tuscany via referral to Versilia Hospital. Once eligibility is confirmed, patients sign an informed consent and are invited for a traditional assessment session with a therapist blinded to their group assignment. Afterwards, patients are randomly allocated to either arm via a random number generator algorithm in blocks of ten. Patients perform daily rehabilitation therapy (5 sessions per week) for 30 min over a 4-week period, for a total of 20 treatment sessions. Subjects assigned to the control group perform 30 min of conventional therapy exercises; patients assigned to the treatment group are subject to 30 min of treatment with the elbow exoskeleton.

Subjects in both groups will undergo both clinical and instrumented evaluations (using the NEEM device) at two time points: pre-treatment (baseline, session T0) and post-treatment (session T1) within 1 week after the end of treatment. Each clinical assessment will include the evaluation of MAS and FMA scores, assessed in blinded fashion. All robotic assessments will include the evaluation of the elbow ROM, as well as other biomechanical and electromyography parameters extracted under different dynamic conditions. Figure 1 represents a scheme of the experimental protocol.

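### FMA level sets the robotic programme and is known before allocation, yet it is neither a named stratification factor nor a term in the primary analysis, which leaves avoidable chance imbalance and loses precision

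*Protocol article*

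**What the plan says.** All references are to the Protocol article.

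- **Who is split.** Study Protocol Design: "The treatment group will be further divided into two levels (sub-groups), based on pathological severity". Level 1 is FMA 28 or lower, Level 2 is FMA above 28. The two levels receive different mixes of passive and active robotic work. Treatment Procedure gives 10 min passive and 2.5 min active-assisted per set for Level 1, and the reverse for Level 2. The control group has one manual programme and no levels.
- **When FMA is known.** Participants and Recruitment: patients are "invited for a traditional assessment session with a therapist blinded to their group assignment. Afterwards, patients are randomly allocated". Treatment Procedure also ties the training level to the initial screening. The level is therefore available at randomisation.
- **How allocation works.** Same section: "patients are randomly allocated to either arm via a random number generator algorithm in blocks of ten", giving patients "randomly allocated either to the control (*n* = 30) or treatment (*n* = 30) group". No stratification factor is named.
- **What is analysed.** MAS and FMA are the primary outcomes, scored at T0 and T1 in both arms. Statistical Analysis names a paired one-way ANOVA on the two time points, with a Mann–Whitney fallback. Baseline differences between groups are tested by chi-squared, and no adjustment follows from that test.

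**The concern.** The plan treats FMA level as important enough to change the intervention, and Study Protocol Design describes the split as one of severity. Eligibility runs from mild to severe deficit, so both levels can be expected in both arms. With only 60 patients, allocation that takes no account of level can by chance give one arm noticeably more severe patients. An analysis with no term for level or baseline FMA cannot correct for that.

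At stake is the precision and credibility of the arm comparison on both primary outcomes. There is a second consequence: because no control sub-groups are defined, the article describes no comparison of either robotic programme with control patients of the same severity. The Discussion nevertheless presents the two-tier classification as part of a core strength of the design.

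**Working it through.** **1. The plan's own figure.** Inputs from Participants and Recruitment: "hypothesis of a post-treatment MAS score reduction of 0.5 points", "from an average of 2.5 ± 0.70 SD at baseline", "with an alpha value of 0.05 and power equal to 80" per cent. Two-sample normal formula, two-sided (sidedness is not stated):

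n per arm = 2(1.96 + 0.84)² × 0.70² / 0.5² ≈ 31.

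At 30 per arm the standard error of the difference is 0.70 × √(2/30) = 0.181, and power is Φ(0.5/0.181 − 1.96) = 79.0%. The stated 30 per group is reproduced to within one patient. The text words the effect as a pre-to-post reduction; that is a separate matter.

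**2. Imbalance under the described allocation.** Six blocks of ten give 30 per arm. If a proportion p of patients is Level 1, the Level 1 counts in the two arms behave as independent Binomial(30, p) variables. Their difference has variance 60p(1 − p). The article gives no value of p, so 0.3, 0.5 and 0.7 are assumed. Results from 200,000 simulated trials per value:

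| Assumed p | P(difference ≥ 4) | P(difference ≥ 6) | P(difference ≥ 8) | 95th percentile |
|---|---|---|---|---|
| 0.3 | 0.324 | 0.120 | 0.033 | 7 |
| 0.5 | 0.366 | 0.155 | 0.052 | 8 |
| 0.7 | 0.324 | 0.120 | 0.033 | 7 |

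Six patients of 30 is 20 percentage points. As a check at p = 0.5: SD = √15 = 3.87, and a normal tail with continuity correction at 5.5/3.87 = 1.42 gives about 0.156.

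**3. Imbalance with stratified blocks of ten.** Within a level, only the last incomplete block can be unbalanced, so the difference cannot exceed 5. Simulation (20,000 trials per p) gives P(≥ 4) of 0.009–0.010, P(≥ 6) of 0, and a 95th percentile of 3.

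**4. What an imbalance does to the estimate.** Suppose the expected change differs by δ between levels. An excess of d Level 1 patients in one arm then shifts the unadjusted arm difference by δ × d/30. For d = 6 this is 0.2δ. The article gives no δ. If δ were as large as the planned effect of 0.5 MAS points (an illustration only), the shift would be 0.1 points, against a standard error of 0.181.

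**5. Do controls of each level exist?** Yes. The 95% range for the number of control patients at FMA 28 or below is 4–14, 10–20 and 16–26 for p = 0.3, 0.5 and 0.7.

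**6. Power within a level, for 0.5 points and SD 0.70.** With 15 per arm: standard error 0.70 × √(2/15) = 0.256, power Φ(0.5/0.256 − 1.96) ≈ 50% (47% by t-test). With 10 per arm: about 36% (33% by t-test).

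**The case against.** **The trial compares strategies.** The stated objective is robotic training against conventional therapy overall. Tailoring one arm by a baseline measure is legitimate, and no per-level claim is planned. This stands, and it is why within-level results should be exploratory only.

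**No controls for either programme.** A reader might infer that Level 1 and Level 2 robotic patients have no matching controls. The article does not support this. Level depends only on FMA measured before allocation, controls have the same measurement, and robotic versus control within a level is still a randomised comparison. It is underpowered, and its numbers are not balanced by design.

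**Bias.** A reader might also infer that the main result is biased. It is not: chance imbalance under randomisation is allowed for in the test's error rate. Using T0 and T1 scores also removes part of any baseline difference. It does not remove a difference between levels in how much patients change, and that is where precision is lost.

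**Stroke phase.** The trial admits patients with a "cerebro-vascular ischemic event in sub-acute (< 6 months) or chronic (> 6 months) phase", and it is tempting to make the same complaint about phase. The article does not say how phase relates to recovery, so phase is left out of this point.

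**A figure near 20%.** Fixing exactly 30 Level 1 patients among 60 gives 19.6% for a difference of 6 or more, but only even differences are then possible. With 29 or 31 the figure is 12.0%. The range of 12–16% is the supportable one.

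**The article is condensed.** The full protocol may name a stratification factor or a covariate. That is possible, and the published description would then need correcting. But the article does describe the allocation procedure down to block size, defines levels in one arm only, and names a primary test that takes no covariate.

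**Conclusion.** The point holds as one of efficiency and balance. A variable that decides the robotic programme, is known before allocation and is the baseline of a co-primary outcome is not used in the allocation or the primary test as described. The arms would differ by 6 or more Level 1 patients in about 12–16% of trials and by 4 or more in about 32–37%, against about 0% and about 1% with stratified blocks.

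These figures rest on an assumed Level 1 prevalence of 30–70%; at 20% prevalence the chance of a difference of 6 or more falls to 7.5%. The effect on the MAS or FMA estimate cannot be sized from the article, because it does not say how change differs by level. The overall comparison remains unbiased and the trial remains interpretable. The change is worth making because it is cheap and uses data already collected.

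**What to change.** 1. Classify every patient in both arms as FMA 28 or below, or above 28, at the pre-allocation assessment.
2. For patients not yet randomised, stratify allocation by that level. Patients already randomised are handled by classification and adjustment in the analysis.
3. Replace the paired one-way ANOVA with a between-arm model of the T1 score, such as ANCOVA, adjusted for the baseline score and FMA level. The Mann–Whitney fallback takes no covariate either; if a rank test is kept, use one stratified by level (van Elteren).
4. Report the robotic-minus-control difference within each level with confidence intervals, labelled exploratory, and state that power is only about 50% for 0.5 MAS points at 15 per arm.
5. If the full protocol already does any of this, correct the published description to match.

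**Cost.** A new allocation list and a change of primary model, which should be fixed before any unblinded look at outcomes. With two strata the last blocks may be incomplete, so the arms may not end at exactly 30 and 30. The sample size is unchanged and no new measurements are needed.

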**Figure 1 F1:**
[figure not shown]
Protocol overview—Treatment Group (TG) patients are divided in two exercise levels based on the upper Fugl-Meyer Assessment (FMA) score. Both groups conduct an initial assessment (T0) followed by 4 weeks−20 days treatment therapy, concluding with an additional assessment session (T1).

### Description of the Robotic Platform

The NEEM is a highly ergonomic powered exoskeleton for elbow mobilization and neurorehabilitation, designed and developed at The BioRobotics Institute (Scuola Superiore Sant'Anna, Pisa), and licensed to its spin-off company IUVO Srl (Pontedera, Italy). In addition to its powered actuation of elbow flexion/extension (F/E) movements, the NEEM includes a 4-degrees-of-freedom (DoF) self-aligning mechanism to accommodate for the laxity of the human elbow joint (31), a height regulation mechanism, and a spherical joint for the positioning of the robot in the workspace (Figure 2).

**Figure 2 F2:**
[figure not shown]
**(A)** NEUROExos Elbow Module platform, including: passive regulations to adjust the height and orientation for each patient; actuation unit; wheeled platform to move the device in the 3-D workspace; graphical user interface (GUI) control via a laptop. **(B)** Detail of the elbow module.

The system offers two working modalities: (1) *Joint position control* mode (“robot-in-charge”), where the robot moves the user's arm through a pre-defined trajectory; (2) *Joint torque control* mode (“patient-in-charge”), in which the robot provides a commanded torque (either assistive or resistive) to the user's arm. When the desired torque is zero, the device works in *transparent mode*, allowing free movement by the user. The NEEM can provide synchronous joint angle-torque recordings in any of its modes.

The present study will use robot-in-charge mode to effect *passive mobilization* of the subject's arm (with no voluntary user input), and patient-in-charge mode (either with the robot providing assistive torque or in the *transparent mode*) for *active mobilization* exercises. Both passive and active ROM (pROM, aROM) are recorded in transparent mode: pROM with the limb manually mobilized by the therapist, and aROM via voluntary movements performed by the subject. The NEEM provides a graphical user interface (GUI) that allows the experimenter to configure the assessment/rehabilitation protocol, according to the therapist's guidance and patient's needs. Exercise instructions and target joint trajectories are displayed to the patient in a dedicated GUI module, appearing on a separate screen (Figure 3).

**Figure 3 F3:**
[figure not shown]
Example of an experimental setup. The patient, donning the exoskeleton and with electrodes positioned on the impaired arm, follows the reference angle (orange) depicted on the screen while keeping the actual joint angle (blue) as close as possible.

The NEEM system can be integrated with an external EMG recording device via a synchronization signal (square wave) routed through a dedicated wired channel, with a maximum delay (uncertainty) of 10 ms. In this study, three EMG channels will be used in the robotic assessment to record muscle activity from the *biceps brachii* (BB), *triceps brachii* (TB), and *brachioradialis* (BR) at a sampling frequency of 1 kHz.

### Experimental Protocol

The protocol is divided into 2 assessment sessions and 20 treatment sessions for both arms of the study, for a total of 22 sessions structured in exercise blocks focused on elbow mobilization.

A robotic mobilization exercise (Figure 4A) includes *N* repeated F/E elbow movements from the maximum angle (θ_max_ - flexed elbow) to the minimum angle (θ_min_ - extended elbow) and vice versa, at a set peak velocity. Between movements, the subject is asked to hold the current angular position (*Static Hold* state), lasting a set time interval of 3 or 5 s, respectively for treatment and assessment exercises. The exercise ends when the number of performed F/E movements *n*_*c*_ reaches the desired value *N*. An optional *Pause* state is present to better suit the performance to the subject's needs: in this case, the system switches to a *transparent* modality, in which the user is free to move and relax; as soon as the subject is ready, the exercise can start anew from the last performed F/E cycle *n*_*c*_.

**Figure 4 F4:**
[figure not shown]
**(A)** Each exercise block consists of ramp/sigmoidal movements from the maximum ROM angle to the minimum, followed by a Static Hold time interval where the patient is asked to maintain the given position. Movement is then inverted and repeated with the same modality until the number of performed cycles **n**_**c**_ equals the desired number of movements *N*. **(B)** Workflow for the robotic assessment and **(C)** treatment procedures.

Exercises are implemented in the form of consecutive training blocks in assessment and treatment sessions, hereby detailed (Figures 4B,C).

### Assessment Procedure

The robotic assessment procedure (Figure 4B) is conducted on the first and within 1 week after the last days of the treatment period. Upon arrival, subjects are informed about the study and the procedures, and sign the consent form. Then they are prepared for the application of the EMG electrodes following the SENIAM guidelines (32). Commercial Ag/AgCl electrodes are placed on the BB, TB and BR muscles, and fixed in place by using tape and sterile dressing. Before fixing the electrodes, visual inspection of the signal is conducted to verify the quality of the signal and that the baseline noise is sufficiently low. Then, the patient dons the exoskeleton with the help of the therapist and the experimenter, and the robot configuration is adjusted to achieve proper fitting with the subject in a comfortable, seated, upright position, with the shoulder in slight flexion (10–30°), slight abduction (10–30°), and internal/external rotation so as to render F/E movements in the approximate sagittal plane.

The assessment procedure starts with the measure of the patient's passive range of motion (pROM). With the device in transparent mode, the therapist moves the affected limb to the maximum and minimum angular positions reached without experiencing resistance to the movement or elicit pain. The difference between the maximum and minimum angular values recorded within three consecutive flexion-extension movements are stored as pROM. An active range of motion (aROM) is then recorded in a similar fashion, during active movements performed by the patient with the device in transparent mode. Elbow mobilization is then performed, consisting of three consecutive exercises: (1) passive quasi-static, (2) passive, and (3) active (transparent mode). The order of the exercises is fixed.

The passive quasi-static exercise includes 5 F/E constant-velocity movements within the pre-recorded pROM, during which the patient is asked to relax as the system mobilizes the limb at 2 deg/s: the main purpose of this exercise is to evaluate muscle and soft tissue resistance to the imposed stretch, by minimizing the contribution of the robot's dynamic and inertial components, which are negligible at constant low speeds.

The passive and active assessment exercises consist of 36 constant-velocity F/E cycles executed at three different velocities (12 cycles per velocity): 40 deg/s, 80 deg/s, 120 deg/s. The velocity order is fixed, and it has been chosen to investigate the occurrence of velocity-dependent spastic contractions of arm muscles. During passive exercises, the patient is asked to relax while the device moves the hindered limb within the pROM. Active exercises, instead, require a dynamic involvement by the patient, who is asked to follow a reference angle on the GUI, moving within the aROM using fully available motor skills.

### Treatment Procedure

The treatment protocol (Figure 4C) lasts for 4-weeks, for a total of 20 sessions. At the beginning of each robotic treatment session, the subject is seated in front of a screen and is helped in donning the exoskeleton with the aid of the therapist and experimenter. The position of the patient with respect to the exoskeleton, as well as the exoskeleton regulations are adjusted to replicate the same configuration as the initial assessment procedure. This will ensure that any variation of biomechanical parameters is not attributed to a different spatial configuration of the patient with respect to the exoskeleton. Due to time restrictions (each session must be conducted within 30 min), treatment sessions do not include EMG recording to maximize the treatment volume.

The treatment procedure starts with the recording of the aROM while wearing the device in transparent modality. Then, a quick (about 2.5 min) passive mobilization is performed within the pROM recorded during the initial assessment procedure (T0), at a fixed velocity of 80 deg/s. Purpose of this mobilization is to have a continuous monitoring of the extracted passive biomechanical parameters through the whole treatment period, with the same conditions as the initial assessment.

The patient is then asked to relax, and a new pROM is recorded with the aid of the therapist. Afterwards, the affected limb is passively moved within this pROM by the exoskeleton via sigmoidal movements at 80 deg/s of peak velocity; the duration of the exercise is set according the training level assigned at the initial screening: 10 min for level 1 patients, 2.5 min for level 2 patients.

Next, the subject is asked to perform an active-assisted exercise in the pROM, by following a reference F/E trajectory in the GUI. The device provides an assistive torque proportional to the error between the reference value and the measured angular value, weighed via a proportional assistance constant *K*_*p*_. A performance index (PI) measure is extracted from each active mobilization block, tying the user's daily performance to the cumulative error in each F/E cycle. The robotic input parameters of passive range of motion (used for both passive mobilization and active exercises) and assistance constant *K*_*p*_are individually adapted to the patient in each session, based on the instrumented measurement of pROM at the start of each session and the PI from the previous two sessions. Specifically, *K*_*p*_ is adjusted (increased or decreased by a set percentage, or else left unmodified) so as to maintain the PI within a moderate range relative to healthy controls, thus representing a “training zone” of functional difficulty where the user remains able to substantially complete the exercises yet is sufficiently challenged to elicit a training effect. The duration of the active-assisted exercise is 2.5 min for level 1 patients, and 10 min for level 2 patients. Two sets of passive and active mobilizations are performed.

At the end of the treatment session, the patient is asked to perform another 2.5 min of passive mobilization within the pROM of the initial assessment, followed by the recording of the aROM without assistance by the device. This procedure is performed to enable evaluation of intra-session changes in movement capacity.

